#### Data analyses

First, for both the effect analyses on the different outcome variables and moderator and mediator analyses, we will perform multiple regression analyses with baseline levels of the outcome variable as a covariate and condition as a predictor variable. Second, to correct for the clustering of participants within regions and within Halt professionals, the regression analyses will be performed in a multilevel model with the participant as level 1, the professional as level 2, and the region as level 3 cluster variables. Third, to correct for multiple testing, we will implement a Benjamini Hochberg False Detection Rate (FDR; (Benjamini & Hochberg, 1995) correction on the p-values for the respective outcome tests. Fourth, to test for the similarity between conditions, we will compare the two groups of Halt professionals and both conditions on several characteristics (e.g., demographic factors, professionals’ educational level, or youths’ psychological problems). If differences are detected between conditions, we will use propensity score matching (PSM) techniques (Caliendo & Kopeinig, 2008) to match participants in the CAU plus YIM condition to participants in the CAU condition. Lastly, we will implement the Intention-to-Treat (ITT) principle for handling missing data on post-test and follow-up measurements (Detry & Lewis, 2014; Yeatts & Martin, 2015). Thus, we will analyse all missing data of participants according to their assigned condition, regardless of whether the intervention was received or completed (Detry & Lewis, 2014; Yeatts & Martin, 2015). Missing data points will be estimated by performing Full Information Maximum Likelihood (FIML) methods. We will consider the percentage of missing data and patterns of missing data (e.g., missing completely at random) (Bennett, 2001; Schulz & Grimes, 2002).

**Power Analysis.** To assess the sample size per condition for the primary and secondary outcomes, we performed an a priori power analysis in G*Power 3.1 (Faul et al., 2009). To attain a power level of 0.80 with a significance level of α = 0.05, a total sample size of *N* = 100 is necessary to detect a small effect size (*f* = 0.10) in a linear multiple regression analysis. Meta-analyses that explored the effects of formal mentoring programs on delinquent behaviour and reoffending revealed small overall effects, both *d* = 0.21 (~ f = 0.10) (Jolliffe & Farrington, 2007; Tolan et al., 2014). For moderator and mediator analysis, a larger sample size is required. We performed a priori power analysis a Monte Carlo Power Analysis (Schoemann et al., 2017, p. 384). For a simple trivariate correlation, a total sample size of *N* = 150 is necessary to attain a power level of 0.80 with a significance level of α = 0.05. This would indicate *N* = 75 per condition. However, we aim to include *N* = 150 per condition because (1) we will also include time as a factor in the moderator and mediation models, and (2) we expect relatively high drop-out rates of over 20% (e.g., drop-out at post-test or follow-up measurements) (Furlan et al., 2009).

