## Methods and design

### Aims and setting

Our main aim is to examine whether YIM strengthens resilience factors, such as perceived social support and social resourcefulness, in delinquent youth. To do so, we will study YIM at Halt, a Dutch juvenile justice system organisation which offers youths a diversion program subsidised by the Ministry of Justice and Security. In the Netherlands, all juvenile offenders (12 to 18 years) are referred to Halt after committing relatively minor offences or crimes (Wolthuis & Stentoumi, 2023). Common offences and crimes include public intoxication, extreme school absenteeism, shoplifting and vandalism. Halt has the nationwide task of providing these youths with a tailored intervention aimed at preventing reoffending and increasing future opportunities (Halt, n.d.). Mainly, Halt works with first- and second-time offenders who remain in the community. Working with 15,000 youths yearly, Halt has a unique position to identify youths (and families) in vulnerable circumstances. These youths are guided towards the necessary formal support systems, such as youth care organisations or addiction treatment centres. Since 2019, 36 Halt professionals (15% of all Halt professionals) have been trained in YIM, allowing YIM-trained professionals to strengthen the informal support system by involving a non-parental adult from the youth’s social network. The Halt program is implemented throughout the Netherlands, but the organisation is organised into four central regions: (1) North-Holland-Centre, (2) North-East, (3) South, and (4) West. Each region has sub-teams supervised by a region manager, and within each region, multiple professionals have been trained in YIM. Of all YIM-trained professionals, 31 (86%) have agreed to collaborate with the YIM-Halt trial. More details on the content of the Halt intervention can be found under “Conditions” > “Care as Usual (CAU) condition”. The quasi-experimental trial (Study 1) and the qualitative study (Study 2) will be performed at Halt and are presented below.

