### Study 1: quasi-experimental trial

#### Design

In this quasi-experimental design, youth referred to Halt are non-randomly allocated to either a non-YIM-trained Halt professional implementing *Care as Usual* (CAU; *N*_*professionals*_ = 31) or a YIM-trained Halt professional implementing *CAU plus YIM* (*N*_*professionals*_ = 31). Even though Halt’s distribution office allocates youth cases to professionals independent of case type and severity, they consider professionals’ workload within each region. This could lead to unequal distribution of youth cases over conditions. To ensure comparable conditions, the two groups of professionals are matched on educational level and region. Thus, despite non-random allocation, we expect similar conditions regarding (1) professionals’ characteristics and (2) case type and severity. Adolescents are our primary informants, but caregiver(s) of youths are also approached. This trial is registered at Clinicaltrials.gov (NCT05555472).

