#### Study sample

Across both conditions, we aim to include 300 juvenile offenders who are (1) between 12 and 18 years old, (2) referred to Halt by either the police, a prosecutor, a special investigating officer, or a school attendance officer, and (3) required to follow a minimum of three meetings at Halt. Thus, so-called ‘shortened cases’, with only 1 or 2 meetings, will be excluded from participation beyond the first measurement (see Fig. 2).

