It is also crucial to mention three potential challenges. First, allocating youths to either condition (i.e., to a non-YIM-trained or YIM-trained professional) is non-random. Random allocation is impossible because Halt’s distribution office considers professionals’ workload. This might lead to an unequal division of youth cases over conditions and, thus, less comparable conditions. Differences between conditions could then possibly be explained by confounding factors instead of the effects of YIM, such as differences in the severity of the youth case (Flannelly et al., 2018). To ensure comparable conditions, we will match professionals in the CAU plus YIM condition within each region to professionals in the CAU condition. Nevertheless, we must be cautious of drawing causal inferences. We will also address other confounding factors between conditions, such as differences in the number of sessions or types of activities. Second, baseline and post-test measurements will occur without the knowledge of the implementation level of YIM in the CAU plus YIM condition. We will assess three levels of implementation steps taken by a professional: (1) the YIM question was asked, (2) steps were taken to support youth in identifying and nominating a YIM, and (3) a YIM was positioned in an official meeting. External factors can influence these steps, such as a youth not being able to identify or nominate a YIM. If this is the case, it is impossible to position a YIM. We will, however, instruct professionals to explain and motivate YIM in all youth cases, possibly leading to the positioning of a YIM. Overall, we expect that all cases will at least have the second level of implementation. However, due to the natural course of YIM, we cannot rule out natural variation in the level of implementation. Because this might impact the findings, we will consider these implementation levels in our analyses. Moreover, these implementation levels will allow us to explore whether different elements of YIM affect the approach’s effectiveness. Third, all participants will voluntarily sign up for the study, potentially leading to a selective pool of more intrinsically motivated participants. Even though Halt has a broad population, with varying degrees of problems and different types and severity of offences and crimes, the registered group might not entirely represent the Halt population. Potentially, youth with more severe problems might be missed. This would, however, apply to both conditions – if this were to be the case. Hence, to appeal to the entire population at Halt, we will offer a monetary contribution per completed questionnaire and the chance to win the grand prize, namely AirPods. Fourth, a challenge in the focus group interviews is that being in a group, people might not feel comfortable enough to share their true perspectives and opinions on working with the innovation. Moreover, some individuals could be more dominant in the conversation than others, which might discourage some individuals from actively participating. To encourage active participation and a comfortable environment, we will perform *think-pair-share* techniques (Kagan, 1994; Lyman, 1981) in a neutral environment without the involvement of YIM and Halt management.

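### Region is modelled as a level-3 cluster with only four units; fixed region terms suit the matched design better, though the gain for the condition test is small

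*Protocol article*

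**What the plan says.** All references are to the protocol article.

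- **Model (Study 1, Data analyses).** The effect, moderator and mediator analyses are "multiple regression analyses with baseline levels of the outcome variable as a covariate and condition as a predictor variable". They are fitted as a multilevel model "to correct for the clustering of participants within regions and within Halt professionals", "with the participant as level 1, the professional as level 2, and the region as level 3 cluster variables". Missing outcomes are handled by full information maximum likelihood.
- **Number of regions (Aims and setting).** "the organisation is organised into four central regions".
- **Matching (Study 1, Design, and Discussion).** "the two groups of professionals are matched on educational level and region". The Discussion adds that "we will match professionals in the CAU plus YIM condition within each region to professionals in the CAU condition", so both conditions should occur in every region.
- **Size.** Of the YIM-trained professionals, "31 (86%) have agreed to collaborate with the YIM-Halt trial". The Design section gives 31 in each condition, so 62 in all. For youths, "we aim to include 300 juvenile offenders".
- **Imbalance.** The Design section says that the distribution office takes workload within each region into account and accepts that this could spread cases unequally over conditions.

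Baseline outcome and condition are the only fixed terms named. In the data analysis section, professional educational level appears only as a characteristic to compare between groups, with propensity score matching to follow if the conditions differ.

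**The concern.** A level-3 cluster in a multilevel model ordinarily means a random effect whose variance is estimated from the units at that level. Here there are four units. They are the organisation's complete set of regions, not a sample from many, and region is one of the two factors on which professionals were matched. A four-unit variance is very imprecise and is often estimated as zero, in which case the model makes no region adjustment. When it is above zero, region effects are shrunk, so region differences are only partly taken out.

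This would matter little if region were perfectly balanced over conditions. Matching balances the professionals, however, not the number of youths each contributes, which depends on workload and voluntary sign-up. If the conditions fill unevenly across regions, part of any additive region difference stays in the estimated effect of condition. The same specification governs every effect, moderator and mediator model.

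**Working it through.** The plan gives no figure for the precision of the region level, so there is none to reproduce.

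**Inputs from the article:** 4 regions; 62 professionals, so 62/4 = 15.5 per region; 300 youths, so 300/62 = 4.84 per professional.

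**Assumed, because the article gives no ICC:** total variance 1; professional ICC 0.05; region ICC ρ of 0.01, 0.02, 0.05 or 0.10; equal cluster sizes. As every model includes the baseline outcome, ρ is best read as what is left after baseline adjustment.

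**Step 1. Precision of a variance on 3 df.** The 95% limits are 3/χ²(3) quantiles times the estimate, i.e. 0.32 to 13.9 times, with coefficient of variation √(2/3) = 82%. For 62 units (61 df) they are 0.72 to 1.48 times, with coefficient of variation √(2/61) = 18%. This treats the true unit means as observed without error, so it is a best case.

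**Step 2. Chance that the region variance is estimated as zero.**
- Variance of a professional's mean within a region: v = 0.05 + (1 − ρ − 0.05)/4.84.
- Ratio of expected mean squares: λ = 1 + 15.5ρ/v.
- P(zero) = P(F(3, 58) < 1/λ) under REML. Under maximum likelihood the bound is about (4/3)/λ.

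For ρ = 0.01: v = 0.05 + 0.94/4.84 = 0.244; λ = 1 + 0.155/0.244 = 1.63; P(F < 0.61) = 39%, and P(F < 0.82) = 51%.

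**Step 3. Share of a region's deviation taken up by the random intercept, variances known.** This is 1 − 1/λ; for ρ = 0.01, 1 − 1/1.63 = 39%.

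| Region ICC | λ | P(zero), REML | P(zero), ML | Share taken up |
|---|---|---|---|---|
| 0.01 | 1.63 | 39% | 51% | 39% |
| 0.02 | 2.28 | 27% | 37% | 56% |
| 0.05 | 4.28 | 13% | 18% | 77% |
| 0.10 | 7.87 | 6% | 8% | 87% |

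Simulation (2,000 runs per scenario, professionals matched within region) agrees: 38%, 27%, 13% and 5% under REML; 50%, 38%, 18% and 7.5% under ML. Fixed indicators take up all of an additive region deviation.

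**Step 4. Effect on the condition test.** Same simulation with no true effect; random region tested with z, fixed region with t. Region ICC runs from 0 to 0.10, and Monte Carlo error is about 0.5 points.

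| Scenario | Type I error, random region (REML or ML) | Type I error, fixed region |
|---|---|---|
| Matched within region | 5.0% to 5.7% | 4.4% to 5.0% |
| Assumed imbalance across regions | 5.0% to 6.8% | 4.3% to 5.4% |

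In the matched scenario the standard deviation of the condition estimate is the same under both models (0.1236 at region ICC 0.05). Under imbalance with a region ICC of zero, random region already gives 6.0% (REML) and 6.5% (ML). With no region differences to confound, that excess cannot come from confounding; z rather than t testing is one source.

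**The case against.** The strongest reply is that the region variance is a nuisance parameter. Condition varies inside every region, so its standard error rests on the 62 professionals rather than on four regions. Step 4 bears this out for the matched design.

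A zero variance is also most likely when regions hardly differ and there is little to remove. Suppose that YIM youths make up 60% in two equal regions and 40% in the other two, with no region adjustment at all. The confounding bias then has SD 0.2√ρ: 0.02 outcome SD at ρ = 0.01 and 0.028 at 0.02, against a sampling SD of about 0.12. At 70/30 it is 0.4√ρ: 0.09 at ρ = 0.05 and 0.13 at 0.10. At those ICCs, though, the random intercept is seldom zero and takes up 77% to 87% of a region's deviation. Baseline adjustment should shrink stable region differences further. All this stands and limits the size of the point.

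Educational level is partly handled by the matching, the planned group comparison and the conditional propensity score step. The article does not use the word random for region, and estimator and degrees of freedom are details that it may leave to a fuller document. The level-3 role of region, however, is a choice it states. If fixed effects were meant, the wording needs correcting.

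A reader might infer that the standard errors for the condition effect are unreliable, or that singular fits will force unplanned model changes. Neither is shown. The simulated mean standard errors lie close to the empirical SDs (for example 0.1227 against 0.1236, REML, matched, region ICC 0.05), and a zero region variance simply leaves youth within professional.

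**Conclusion.** The point holds as a modest improvement to a stated modelling choice. Four regions cannot support a usable level-3 variance: 3 df, and a zero estimate in about 39% to 6% of trials (51% to 8% under ML) for region ICCs of 0.01 to 0.10. The random intercept removes additive region differences only in part.

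The consequence for the condition test is small while matching within region holds. It becomes relevant only if the conditions fill unevenly across regions, which the article itself allows for. Even then the simulated type I error was at most 6.8%, and not all of that is due to region.

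These figures rest on assumed ICCs, equal cluster sizes, an assumed imbalance pattern, and the reading of a level-3 cluster as a random effect. It would also go too far to say that fixed terms remove region differences fully: they remove additive differences between these four regions, not a condition effect that differs by region.

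**What to change.** Fit a two-level model, youth within professional, in every effect, moderator and mediator analysis:

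- Keep professional as a random level, because condition is assigned there.
- Replace the region level by three fixed indicators.
- Add professional educational level, the other matching factor, as a fixed covariate.
- Test condition with Satterthwaite or Kenward-Roger degrees of freedom based on the 62 professionals.

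**Cost.** This is a change of wording plus a few degrees of freedom. Four region means and one condition term leave about 62 − 5 = 57 at professional level, less those used by educational level. In the simulation, fixed region terms cost no precision in the matched design. Under the assumed imbalance they raised the SD of the condition estimate by at most about 3% (0.1308 against 0.1270 under REML, at a region ICC of zero). If differences in the YIM effect between regions are of interest, they need a separate region-by-condition analysis.

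### Participant-level confounder control beyond the baseline outcome applies only if a baseline difference is detected, although allocation is non-random and no detection criterion is given

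*Protocol article*

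**What the plan says.** The Design section of Study 1 states that allocation is non-random. The distribution office assigns cases without regard to case type or severity, but it does take workload into account. The section adds: "This could lead to unequal distribution of youth cases over conditions". The Discussion names the consequence: "Differences between conditions could then possibly be explained by confounding factors instead of the effects of YIM".

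Two safeguards apply whatever the data show. In Design, "the two groups of professionals are matched on educational level and region". In Data analyses, the effect models are "multiple regression analyses with baseline levels of the outcome variable as a covariate and condition as a predictor variable", fitted with professional and region as higher levels.

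Anything further at participant level is conditional. Data analyses says "we will compare the two groups of Halt professionals and both conditions on several characteristics", with the characteristics given by example only. It continues: "If differences are detected between conditions, we will use propensity score matching (PSM) techniques", used "to match participants in the CAU plus YIM condition to participants in the CAU condition". The article gives no threshold for detection, no closed list of confounders, and no matching ratio, caliper or replacement rule. The same section says data are analysed "according to their assigned condition, regardless of whether the intervention was received or completed".

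**The concern.** In a quasi-experiment, confounding is the main threat to the primary estimate. A rule that adjusts only after a difference has been detected treats non-detection as balance. A sample of this size has little chance of detecting an imbalance about as large as the effect being sought, so the default estimate can carry bias from a confounder that was measured and could have been adjusted for. The rule can also fire by chance when nothing is out of balance. Whether matching is done, and possibly which youths are analysed, then depends on a noisy preliminary step.

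This is not a complaint about detail left to an analysis plan. The conditional rule is stated in the article and is the wrong rule for a non-randomised comparison.

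**Working it through.** The plan gives no figure for the balance check, so there is none to reproduce. Its stated total of N = 100 is a separate matter and is not used here.

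**Inputs from the protocol article**
- 150 participants and 31 professionals per condition (Conditions; Design).
- α = 0.05, planned d = 0.21, drop-out over 20% (Power Analysis). At 20%, 150 × 0.80 = 120 per condition. This smaller number applies if the check is run on those who remain.

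**Assumptions, not in the article**
- *Detected* means two-sided p < 0.05.
- Intraclass correlation (ICC) per professional of 0 or 0.05.
- True imbalance of 0.1 to 0.3 SD in one confounder.
- Standardised confounder–outcome slope of 0.3 to 0.5, given the baseline outcome.

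**1. Chance that the check detects a true imbalance δ**

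Power ≈ Φ(δ / √(2·DE/n) − 1.96), with DE = 1 + (n/31 − 1) × ICC. At ICC 0.05, DE is 1 + (4.839 − 1) × 0.05 = 1.192 for n = 150, and 1 + (3.871 − 1) × 0.05 = 1.144 for n = 120.

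For δ = 0.2, n = 150, ICC 0: √(2/150) = 0.1155; 0.2/0.1155 = 1.732; Φ(1.732 − 1.96) = 0.41.

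| δ | n=150, ICC 0 | n=150, ICC 0.05 | n=120, ICC 0 | n=120, ICC 0.05 |
|---|---|---|---|---|
| 0.10 | 0.137 | 0.122 | 0.118 | 0.108 |
| 0.20 | 0.410 | 0.354 | 0.341 | 0.305 |
| 0.30 | 0.738 | 0.663 | 0.642 | 0.584 |

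A 0.2 SD imbalance is therefore missed with probability 1 − 0.410 = 0.59 to 1 − 0.305 = 0.695. The imbalance detectable with 80% power is (1.96 + 0.8416) × √(2·DE/n), which runs from 0.32 SD (n = 150, ICC 0) to 0.39 SD (n = 120, ICC 0.05).

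**2. False triggers**

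With K independent checks and no true difference, the chance of at least one detection is 1 − 0.95^K: 0.23 for K = 5, 0.40 for K = 10 and 0.64 for K = 20.

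**3. Bias left by the rule**

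This was simulated with 3,000 runs per setting, no true effect, one confounder, the baseline outcome always in the model and no clustering. Regression adjustment stood in for matching. Selected settings, including the extremes (bias in SD units):

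| n per arm | δ | slope | detected | never adjust | rule, undetected trials | rule, average | always adjust |
|---|---|---|---|---|---|---|---|
| 150 | 0.1 | 0.3 | 0.135 | 0.027 | 0.017 | 0.015 | −0.004 |
| 150 | 0.2 | 0.5 | 0.411 | 0.102 | 0.063 | 0.038 | 0.002 |
| 150 | 0.3 | 0.3 | 0.733 | 0.092 | 0.041 | 0.014 | 0.002 |
| 120 | 0.2 | 0.5 | 0.335 | 0.103 | 0.065 | 0.045 | 0.003 |
| 120 | 0.3 | 0.5 | 0.640 | 0.151 | 0.085 | 0.030 | 0.000 |

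Over all settings the average bias of the rule is 0.014 to 0.045 SD: 0.014/0.21 = 7% and 0.045/0.21 = 21% of the planned effect. In undetected trials it is 0.017 to 0.085 SD (8% to 40%). Always adjusting gives −0.004 to 0.004. Type I error under the rule stayed between about 0.04 and 0.06.

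**4. Loss of youths, only if matching is 1:1 with a caliper and without replacement**

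With a caliper of 0.2 SD of the logit propensity score and three of six covariates shifted by 0.2 to 0.4 SD, 150 per arm gave 120.3 to 105.2 pairs (19.8% to 29.9% lost), and 120 per arm gave 93.3 to 83.3 (22.3% to 30.6% lost). A second simulation, with a single propensity shift of 0.2 to 0.5 SD at 120 per arm, kept 101 to 92 pairs: 1 − 101/120 = 16% and 1 − 92/120 = 23% lost. In the first simulation, unadjusted two-group power at d = 0.21 falls from 0.44 to 0.33–0.37 (150 per arm) or from 0.37 to 0.27–0.30 (120 per arm).

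**The case against.** The strongest defence is that the plan already controls a good deal unconditionally. The baseline outcome is in every model, professionals are matched on education and region, and both cluster levels are modelled. Cases are said to be distributed without regard to type or severity apart from workload, so a true 0.2 SD imbalance may not exist. The Discussion also urges caution about causal claims. All of this stands, and it narrows the point to confounding beyond these safeguards. It does not rescue the trigger: the article itself names unequal case mix as a risk, a random intercept for professional models clustering without removing differences between conditions, and caution does not correct an estimate.

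A reader might infer several stronger points that the document does not support:
- *All confounding control is conditional.* It is not, for the reasons above.
- *Matching must discard youths and so breaks intention to treat.* The article says only that propensity matching techniques will be used. Full or kernel matching can keep most or all youths, and matching reassigns nobody. The conflict arises only if youths are dropped.
- *Differences between professionals cannot be handled.* The two groups of professionals are to be compared, and nothing bars their characteristics from the propensity score.
- *Bias of 29% to 48% of the planned effect.* At 0.2 SD × slope 0.3 to 0.5 = 0.06 to 0.10 SD, that is the bias if adjustment never happens, not the bias of this rule.

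**Conclusion.** The concern holds in a limited form. In a non-randomised trial, participant-level confounder control beyond the baseline outcome rests on an undefined detection step. Read as p < 0.05, that step misses a 0.2 SD imbalance in about 59% to 70% of trials and, with ten independent checks, fires falsely about 40% of the time.

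The average bias per confounder is modest, but not negligible against d = 0.21, and it could add up over several confounders. These sizes rest on the assumed threshold, ICC, imbalances and slopes. The loss of 16% to 31% of youths, and the tension with analysis by assigned condition, hold only under the matching variant simulated.

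Confounders that were never measured remain a limitation under any of these approaches.

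**What to change.** Delete the condition that a difference must first be detected. In every effect model, adjust for a prespecified set of pre-intervention covariates: demographics, offence and referral information, baseline SDQ problems, the baseline outcome and the professional's work experience. Tables 1 and 2 list all of these as collected. Region is already a model level.

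Keep the set to variables fixed before the intervention starts. The number of sessions and types of activities, which the Discussion gives as confounders to be addressed, arise after allocation and do not belong in it.

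Describe balance with standardised differences rather than tests. Keep propensity matching or weighting as a preplanned sensitivity analysis and state the algorithm. The choice between them is partly preference, since overlap weighting also changes the target population.

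The cost is a few degrees of freedom and a change of plan wording; no new data are needed.

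### As written, FIML for the main effect analyses adds nothing over a baseline-adjusted complete-case analysis unless post-test and follow-up share one likelihood or auxiliary variables are included

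*Protocol article*

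**What the plan says.** All of this is in the Protocol article, Study 1.

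- **Effect model (Data analyses).** The analyses are "multiple regression analyses with baseline levels of the outcome variable as a covariate and condition as a predictor variable".
- **Levels (Data analyses).** Clustering is handled with "the participant as level 1, the professional as level 2, and the region as level 3 cluster variables". No level for measurement occasion is named.
- **Missing data (Data analyses).** Intention-to-treat is invoked for "handling missing data on post-test and follow-up measurements", followed by "Missing data points will be estimated by performing Full Information Maximum Likelihood (FIML) methods". The section adds: "We will consider the percentage of missing data and patterns of missing data". It attaches no consequence to what is found.
- **Drop-out (Power Analysis paragraph).** The authors write "we expect relatively high drop-out rates of over 20"%, at post-test or follow-up, and give this as one reason for the target: "However, we aim to include *N* = 150 per condition". Time as a factor is mentioned there for the moderator and mediation models only.
- **Timing (Data collection and procedure).** Consent leads straight to the baseline questionnaire. The post-test comes at 100 days and the follow-up at nine months.

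**The concern.** FIML uses incomplete cases only through variables that are in the likelihood and are observed for those cases. If a model holds one outcome wave, condition and baseline, a youth whose outcome is missing has nothing further to offer. The plan's wording suggests that drop-outs are recovered. Under this model they are simply left out of the estimate.

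The follow-up comparison is the most exposed. It is nine months out, and the Discussion accepts that participants may be a self-selected, more motivated group and that YIM will be implemented to different degrees. Drop-out that is related to how a youth was doing at the post-test, and that differs between conditions, is therefore plausible. The post-test score would carry information about such youths, but a single-wave model does not use it.

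**Working it through.** There is no plan figure to reproduce: the drop-out rate is an assumption, not a derived number. At exactly 20% drop-out, 300 x 0.80 = 240 youths would have an outcome.

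**1. Algebra.** Let X be condition and baseline, both observed, and Y the outcome at one wave. Since f(Y, X) = f(Y | X) f(X), a case with Y missing contributes only f(X), which does not contain the condition effect. The multilevel likelihood behaves the same way. For professional j it is the integral over the random effect u of the product of f(y_ij | x_ij, u); integrating out a missing y_ij replaces its factor by 1. The region level adds one more integral of the same kind.

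**2. Numerical check.** In one simulated dataset with 17.7% of outcomes missing, complete-case regression and FIML both gave 0.1725 for condition and 0.5275 for baseline. Over 3 x 1,500 = 4,500 datasets, the largest difference between the two condition effects was below 2e-10.

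**3. When the stated analysis is valid, and when it is not.** Assumptions for set A (mine, not the plan's): N = 300, no clustering; b = baseline, c = condition, p = post-test, f = follow-up.

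- p = 0.5b + 0.21c + 0.85e
- f = 0.2b + 0.5p + 0.105c + 0.8e'
- True effect on f given b: 0.105 + 0.5 x 0.21 = 0.21

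The 0.21 is borrowed from the d in the Power Analysis paragraph. Only follow-up values were deleted; 1,500 datasets per row.

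| Log-odds of drop-out at follow-up | Missing | Unadjusted completers | Adjusted complete case = single-wave FIML | FIML with post-test |
|---|---|---|---|---|
| -1.5 - 1.0b + 0.5c | 26% | 0.240 | 0.211 | 0.211 |
| -1.5 - 1.0b(1 - 2c) | 22% | 0.040 | 0.211 | 0.210 |
| -1.6 - 1.2p(1 - 2c) | 24% | -0.063 | 0.035 | 0.211 |

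Rows 1 and 2: when drop-out depends on baseline and condition, the stated analysis is unbiased, even where the raw completer contrast is badly wrong. Row 3: when drop-out depends on the post-test in opposite directions by arm, the bias is 0.035 - 0.21 = -0.175 SD.

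**4. A milder mechanism (set B).** N = 300, true effect 0.21, residual correlation 0.6 between post-test and follow-up, no clustering, 4,000 trials per scenario. Drop-out depends on the post-test in the YIM arm only.

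| Log-odds per SD of post-test | Drop-out | Stated analysis | Bias |
|---|---|---|---|
| -0.5 | 20% | 0.253 | +0.043 |
| -0.5 | 29% | 0.270 | +0.060 |
| -1.0 | 20% | 0.294 | +0.084 |
| -1.0 | 30% | 0.323 | +0.113 |

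The joint post-test and follow-up likelihood gave 0.209 to 0.211 throughout. As a share of 0.21, the bias runs from 0.043/0.21 = 20% to 0.113/0.21 = 54%.

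**5. Precision.** Where the stated analysis is unbiased, the joint model gains little: 0.1207/0.1173 = 1.03 (set A, row 1), 0.1199/0.1157 = 1.04 (row 2), and 0.120/0.114 = 1.05 under completely random 30% drop-out (set B).

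**6. Limit of the joint model.** A youth lost before the post-test has both outcomes missing. By step 1 that youth again contributes nothing to a joint model of the two waves. Only auxiliary variables can help there.

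**The case against.** - **A reader might infer that FIML gives no protection here at all. The documents do not support that.** Baseline adjustment is part of the stated model, and rows 1 and 2 of set A show it removing the bias when drop-out depends on baseline and condition. Drop-out may also depend on further variables without bias, provided they do not predict the outcome given the model's covariates.
- **Separate models per wave are inferred, not stated.** A participant at level 1 also fits a wide-format model with both waves as outcomes, in which FIML would use the post-test of a youth lost at follow-up. The sentence describing the regressions covers the moderator and mediator analyses too and mentions no time factor, yet the Power Analysis paragraph puts time into those models. So the description is incomplete. This stands as a limit on certainty. Still, no occasion level is named and time is not mentioned for the effect analyses, so one wave per model remains the natural reading.
- **Auxiliary variables may be set out in a fuller document.** That is possible, and their absence from an article is not in itself a fault. The point is that the method the article does state does not do what its wording says.
- **FIML has a real role elsewhere in the plan.** Mediators, or any missing baseline values, can make FIML differ from complete-case analysis. This stands; the point concerns the main effects with only the outcome missing.
- **The sizes rest on chosen mechanisms.** This stands. The set B biases are also below the standard error of about 0.12. The target of 150 per condition allows for loss (75/0.80 = 94), but a larger sample does not remove bias.

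**Conclusion.** The point holds in a limited form. For the main effect analyses as described, with one outcome wave per model and only the outcome missing, FIML is the same as baseline-adjusted complete-case analysis. This is exact and needs no assumption about the drop-out mechanism.

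That analysis is sound if drop-out depends only on condition and baseline outcome. Otherwise it can be biased at follow-up, with size and direction set by the mechanism: +0.04 to +0.11 SD in one family of assumptions and -0.175 SD in another, on a true 0.21. A reader might infer that the YIM effect will be inflated, or deflated; nothing in the article supports predicting either. The simulations ignored clustering and deleted follow-up values only, so they show the vulnerability rather than forecast the bias.

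This is an inexpensive improvement to make before analysis. It does not show that the planned analysis is invalid.

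**What to change.** State which of these applies to the main effect analyses.

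1. **Joint model (preferred).** For each outcome, fit post-test and follow-up in one likelihood, either with occasion within youth within professional or in wide format with both waves as outcomes. Include condition by time and baseline by time, let the two waves' residuals correlate freely, and report the condition effect at each wave.
2. **Per-wave models with auxiliary variables.** Keep the regressions, but bring the other wave, the caregiver version of the scale where there is one, baseline SDQ and Halt registration data into the FIML likelihood. They should enter as auxiliary variables and not as predictors, because adjusting for the post-test would change the meaning of the follow-up condition effect.

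Adding the caregiver, SDQ and registration variables to option 1 as well would help with youths lost before the post-test, who gain nothing from the second wave. The missing-data sentence should then say what missing-at-random is conditional on.

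The cost is revised wording and a few more parameters; Table 1 and the registration data already supply the variables. The gain is a weaker missing-at-random assumption at follow-up and, in the simulations above, about 3-5% in standard error where the stated analysis is already unbiased.
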